## Abstract

**Background/Objectives:** Stroke remains a leading cause of disability in Japan, and early mobilization is an important strategy to prevent muscle atrophy and promote independence. However, the optimal intensity and duration of early rehabilitation remain unclear. This study aims to examine the association between rehabilitation dose during the acute phase of stroke and functional outcomes at 90 days post-onset. **Methods:** This multicenter prospective cohort study will enroll patients from twelve acute care hospitals across Japan, beginning in June 2026. Eligible patients are aged ≥ 18 years, expected to be hospitalized for ≥7 days, and initiated rehabilitation by day 2 after stroke onset. Rehabilitation dose will be quantified using the Mobilization Quantification Score (MQS). The primary outcome is functional status measured by the modified Rankin Scale (mRS) at 90 days. Secondary outcomes include muscle atrophy assessed by ultrasound, the Barthel Index, and physical performance measures. Subgroup analyses will evaluate how stroke severity modifies the dose–response relationship. **Results:** As this is a study protocol, results are not yet available. The study is designed to clarify the relationship between early rehabilitation dose and functional recovery after stroke. **Conclusions:** This is the first large-scale Japanese study to assess early stroke rehabilitation dosage using a standardized tool. Findings are expected to provide evidence for individualized, evidence-based mobilization strategies to optimize functional outcomes in stroke patients.

## 1. Introduction

Stroke is a leading cause of disability worldwide [1] and ranks fourth among the top ten causes of death in Japan. Although advances in medical science have improved survival rates for patients with severe stroke in recent years, the number of individuals living with long-term physical and cognitive sequelae has increased [2,3]. Among these, muscle atrophy in the paralyzed limbs of patients with hemiplegia, referred to as central atrophy, significantly affects both functional independence and quality of life [4]. In addition to stroke-related disability, critically ill patients may experience other complications, such as intensive care unit (ICU) acquired weakness, characterized by generalized weakness of the limbs and respiratory muscles, further impeding recovery [5,6]. Skeletal muscle atrophy in severely ill patients progresses rapidly by approximately 2% per day, amounting to a 12% reduction in muscle mass per week, and is directly associated with loss of functional independence and reduced quality of life. Therefore, early detection and prevention of muscle atrophy are crucial [7].

Rehabilitation is a primary strategy to promote functional recovery and enhance independence in stroke patients [8]. Once the patient’s neurological symptoms and vital signs stabilize during the acute phase, those with functional impairments transition to the post-acute phase and begin rehabilitation. Traditionally, active rehabilitation has been implemented during the post-acute phase, when patients are medically stable, with the goal of minimizing long-term disability [9]. More recently, increasing attention has been paid to early mobilization in critically ill patients. While several studies have reported the safety of early mobilization, its effectiveness remains a subject of debate [10]. Several systematic reviews and guideline papers have highlighted both the potential benefits and uncertainties of very early mobilization after stroke, noting variability in outcomes depending on patient severity, timing, and dose of interventions [11,12,13]. For example, one study reported that very early mobilization was associated with poorer functional outcomes and higher rates of adverse events at 3 months post-stroke compared to standard care [14]. However, a post hoc analysis of the same cohort revealed that patients who received shorter and more frequent mobilization sessions had significantly improved functional outcomes [15].

Previous research investigating the impact of early mobilization has examined patient outcomes in relation to age, stroke severity, and specific rehabilitation parameters, including intensity, duration, frequency, and timing of interventions [16,17,18]. It has also been suggested that optimal rehabilitation parameters should be tailored to the individual’s disease status and clinical characteristics [19]. Furthermore, considering both intensity and duration as components of physical activity may enable a more precise quantification of rehabilitation interventions, potentially leading to optimized clinical outcomes [13]. The acute phase of stroke is characterized by hemodynamic instability, rapid neurological deterioration, and accelerated skeletal muscle wasting, which can begin within hours of onset and progress by approximately 2% per day in severely ill patients [7]. During this period, patients are also at high risk for complications such as pneumonia, deep vein thrombosis, and pressure ulcers, all of which are exacerbated by immobility [9]. Therefore, timely initiation of rehabilitation is considered crucial not only to prevent secondary complications and muscle atrophy but also to maximize the potential for neurological recovery. This critical window highlights the need to carefully evaluate the appropriate dose and timing of early mobilization interventions. However, there is currently no consensus on the ideal dose, intensity, or timing of early mobilization for stroke patients in the acute phase. Each healthcare facility is thus exploring these parameters independently in pursuit of best practices [11]. Notably, there have been no large-scale studies in Japan evaluating the optimal daily dose of rehabilitation for stroke patients, nor have there been investigations focusing on the dosage of early-stage rehabilitation interventions.

Despite growing interest in early mobilization after stroke, key uncertainties remain. First, the optimal dose and timing in the acute phase are unresolved, with heterogeneous and sometimes conflicting results [14,15,20]. Second, most studies lack a standardized, quantitative dose metric, limiting cross-study comparability; the Mobilization Quantification Score (MQS) addresses this by integrating mobilization level and duration [16,21]. Finally, early-phase studies rarely incorporate objective muscle-atrophy assessments (e.g., rectus femoris ultrasound) despite prognostic relevance [7,22]. We hypothesize that the optimal rehabilitation dose during the acute phase of stroke varies by stroke severity: higher-intensity mobilization may promote greater independence in activities of daily living at 90 days post-stroke in patients with mild strokes, whereas lower-intensity mobilization may be more beneficial in those with severe strokes. We hypothesize that a higher early rehabilitation dose will be associated with better functional outcomes at 90 days. We further hypothesize that baseline stroke severity modifies this association: patients with mild-to-moderate stroke will benefit from higher MQS [21], whereas patients with severe stroke may benefit from moderate doses. Secondary hypotheses are that higher MQS will be associated with less rectus femoris muscle atrophy on ultrasound and better performance on physical assessment. To test this hypothesis, we will use the MQS to assess rehabilitation dose. In addition, we will analyze patient background characteristics, nutritional status, muscle atrophy, and differences in rehabilitation protocols across participating facilities. This study aims to establish standardized and optimized early mobilization practices and to evaluate the relationship between MQS-based rehabilitation dosage and functional independence in stroke patients.

## 2. Methods

This study protocol is reported in accordance with the Standard Protocol Items: Recommendations for Interventional Trials checklist (see Supplementary Materials Table S1).

### 2.1. Study Design

This is a multicenter, prospective, observational cohort study with a 90-day follow-up. The study will begin with the enrollment of the first patient and continue until the 90-day follow-up of the last enrolled participant. Twelve acute care hospitals across Japan will participate. Enrollment is scheduled to begin in June 2026 and continue for 18 months.

### 2.2. Ethical Approval

The study protocol has been approved by the Ethics Committee of Gifu Health Science University (approval number: 2025-012). All participating institutions will obtain approval from their respective ethics committees before patient recruitment. The study will be conducted in accordance with the Declaration of Helsinki and relevant Japanese ethical guidelines. Written informed consent will be obtained from all patients or their legally authorized representatives (e.g., next of kin) within 24 h of admission, if not already obtained during hospitalization. The study has been registered with the University Hospital Medical Information Network (UMIN000057876).

### 2.3. Study Setting

Twelve regional acute care hospitals in the Chubu region will participate (Supplementary materials Figure S1). Institutional characteristics (including the presence of unique clinical protocols, nurse-to-patient ratios, and availability of neurologists or other specialists) will be documented prior to enrollment and remain fixed throughout the study period. Rehabilitation practices vary among institutions but are based on standard references, including the Stroke Treatment Guidelines [20], Japanese Guidelines for Rehabilitation of Critically Ill Patients [23], and the Japanese Guidelines for Nutrition in Critically Ill Patients [24].

All hospitalized stroke patients will be screened within 24 h of admission by the research staff or departmental rehabilitation teams on working days. Eligible patients (if awake and cooperative) or their family members will be approached for consent within the first 24 h of admission, after which data collection will begin (Table 1).

### 2.4. Timeline

After enrollment in the BRIDGE cohort, patients will remain in the study until loss to follow-up or completion of the 90-day assessment post-onset. Data will be collected at four time points: (1) enrollment, (2) day 7 of hospitalization, (3) hospital discharge, and (4) 90 days after stroke onset (Figure 1).

### 2.5. Participants

a. Inclusion criteria:Patients diagnosed with acute stroke, specifically including ischemic stroke (cerebral infarction) and hemorrhagic stroke (intracerebral hemorrhage), who are expected to be hospitalized for ≥7 days. Patients with subarachnoid hemorrhage or transient ischemic attack (TIA) will be excluded because their rehabilitation course differs substantially from that of ischemic and hemorrhagic stroke;Age ≥ 18 years;Provision of informed consent;Initiation of rehabilitation by day 2 of admission.

b. Exclusion criteria:Pre-hospitalization mRS ≥ 3 (unable to walk even with aids);Terminal care patients or those with non-curative intent;Patients with anticipated prolonged immobility due to trauma (e.g., multiple unstable fractures, burns, amputations);Inability to communicate in Japanese;Explicit refusal to allow use of clinical data for research.

c. Anticipated cohort characteristics and planned reporting.

Based on stroke case-mix in the participating hospitals, we anticipate a sex distribution of approximately 55–60% male and 40–45% female, with a mean age around 70 years. For transparency and comparability, we predefine age strata as <65, 65–79, and ≥80 years. Baseline characteristics will be summarized overall and, where appropriate, by sex and age group.

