### 2.6. Primary Outcome

The primary outcome is the modified Rankin Scale (mRS) score at 90 days post-stroke. The mRS ranges from 0 (no symptoms) to 6 (death) and is the most widely used functional outcome measure in stroke trials [25]. An mRS ≤ 2 at 90 days is defined as a favorable outcome (Table 2).

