### 2.12. Data Management and Follow-Up

Patient data will be managed in compliance with Japanese data protection guidelines. A unique study number will be assigned upon enrollment. Follow-up assessments will be conducted via telephone at 90 days post-onset, collecting data on survival, employment, and mRS. If unreachable after multiple attempts, patients will be considered lost to follow-up. Informed consent includes potential secondary use of anonymized data, contingent on new ethical approval.

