### 2.13. Rehabilitation Dose

Rehabilitation dose is defined using the MQS over days 1–7 post-admission. MQS combines mobilization level (assessed using the ICU mobility scale [33]) and duration (measured with a stopwatch). Only active mobilization time is included; preparation or rest is excluded. The MQS is averaged across the first 7 days to reflect the daily rehabilitation dose (Japanese version MQS [21]. It should be noted that rehabilitation itself continues beyond the first 7 days until hospital discharge, according to each institution’s standard practice. After discharge, patients typically continue rehabilitation in post-acute care facilities or outpatient/community settings, depending on their medical condition and regional healthcare resources. Functional outcomes at 90 days will therefore reflect the combined effect of early inpatient rehabilitation and subsequent standard care.

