### 2.14. Statistical Methods

There is no maximum sample size for this study; however, the outcome may be subject to targets or maximum sample sizes, which will be specified in the relevant sub-protocol. The expected sample size is ≥200 patients (minimum 10 patients/facilities, ≥20 facilities) to provide a sufficient number of different rehabilitation doses to predict functional outcomes and build robust models for protocol use. To avoid over-representation of some centers, data collection is limited to 50 patients per facility. Patient enrollment will therefore not be strictly equal across hospitals; each facility is expected to enroll at least 10 patients, with a maximum of 50 patients, depending on their clinical volume. This strategy ensures diversity in practice patterns while preventing over-representation of any single center. The number of enrolled patients and facilities is a sufficient sample size to capture the various variations in practice and treatment. It is considered feasible to collect a sample of this calculated size because each participating facility should be able to enroll at least one patient per month based on the number of stroke patients hospitalized at each facility in the past.

Baseline characteristics and outcomes will be summarized using descriptive statistics. Continuous variables will be presented as means with standard deviations (SDs) or medians with interquartile ranges (IQRs), while categorical variables will be presented as frequencies and percentages (*n*, %).

The primary analysis will examine the association between the mean rehabilitation dose (MQS score) during the first 7 days of hospitalization and the primary outcome of a favorable functional outcome (mRS ≤ 2) at 90 days. This association will be evaluated using a multivariable logistic regression model. The model will be adjusted for a pre-specified set of covariates selected for their established prognostic significance, including age, sex, pre-admission mRS, baseline National Institutes of Health Stroke Scale (NIHSS) score, stroke subtype (ischemic or hemorrhagic), and participating facility (as a random effect).

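### The Abstract counts the day-2 rehabilitation criterion from stroke onset and Section 2.5 counts it from admission; separately, the dose window runs from admission, the outcome from onset, and the named covariates omit the delay between them

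*Protocol article*

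**What the plan says.** The article states the start-of-rehabilitation criterion twice, with different anchors:

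- Section 2.5 (Participants), inclusion criteria: "Initiation of rehabilitation by day 2 of admission".
- Abstract, Methods: eligible patients "initiated rehabilitation by day 2 after stroke onset".

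No other section reconciles the two. Elsewhere, entry and exposure are counted from admission:

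- Section 2.3: "All hospitalized stroke patients will be screened within 24 h of admission".
- Section 2.13: "Rehabilitation dose is defined using the MQS over days 1–7 post-admission".
- Section 2.14: the primary analysis uses "the mean rehabilitation dose (MQS score) during the first 7 days of hospitalization".
- Table 1 places T0 and the cohort index date at hospital admission.

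The outcome is counted from the stroke:

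- Section 2.6: "The primary outcome is the modified Rankin Scale (mRS) score at 90 days post-stroke".
- Section 2.12: "Follow-up assessments will be conducted via telephone at 90 days post-onset". Section 2.4 uses the same anchor.

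The covariates named for the primary logistic model in Section 2.14 are age, sex, pre-admission mRS, baseline NIHSS, stroke subtype and facility (as a random effect). Time from onset to admission is not among them.

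**The concern.** There are two linked issues.

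First, the two eligibility sentences define different cohorts. A patient who reaches hospital after the day of onset and starts rehabilitation promptly can satisfy Section 2.5 and fail the Abstract. A reader of the eventual results could not tell from the article which population was intended.

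Second, with exposure anchored to admission and outcome to onset, the same days 1–7 dose is measured at different times after stroke in different patients. The Introduction itself treats time since onset as important. It describes early instability and deterioration, muscle wasting that can start within hours, and a critical window for dose and timing. If later arrivals differ both in how much mobilization they can tolerate and in prognosis, the delay confounds the dose–outcome association. Baseline NIHSS covers only part of this. Section 2.8 records it at admission, so in a late arrival it is itself measured later after the stroke. The same score defines the severity categories for the planned interaction in Section 2.14.

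The issues meet in the eligibility sentence, because the clock chosen there decides how much delay can enter the cohort.

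**Working it through.** The article gives no figure to reproduce; the check is day counting.

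**Inputs.** Section 2.5 (start by day 2, from admission); Abstract (start by day 2, from onset); Sections 2.13 and 2.14 (dose over days 1–7 from admission); Sections 2.4, 2.6 and 2.12 (outcome at day 90 from onset). Let k be whole days from onset to admission and d the hospital day on which rehabilitation starts. The article gives no values for k, so those below are illustrative. The stroke is assumed to begin on or before the day of admission; an in-hospital stroke would reverse the ordering and is not addressed.

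**Step 1: where the eligibility rules disagree.** The admission rule is d ≤ 2. The onset rule is d + k ≤ 2. The article does not say whether the first day is day 1 or day 0, so both are shown for patients who meet the admission rule.

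| Delay k | First day = day 1 (d = 1, 2) | First day = day 0 (d = 0, 1, 2) |
|---|---|---|
| 0 | rules agree | rules agree |
| 1 | disagree if d = 2 (1 + 2 = 3) | disagree if d = 2 (1 + 2 = 3) |
| 2 | disagree for every d (2 + 1 = 3 at the earliest) | disagree if d = 1 or 2; agree if d = 0 |
| 3 or more | disagree for every d | disagree for every d |

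Since k ≥ 0, anyone who meets the onset rule also meets the admission rule. Section 2.5 is therefore the broader criterion.

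**Step 2: where the dose window falls.** With the day of onset as day 1 for a patient admitted that day, the window in post-stroke days is (k + 1) to (k + 7). The gap from its end to the outcome is 90 − (k + 7) = 83 − k days.

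| k | Post-stroke days covered by MQS | Gap to day 90 |
|---|---|---|
| 0 | 1–7 | 83 |
| 1 | 2–8 | 82 |
| 3 | 4–10 | 80 |
| 5 | 6–12 | 78 |
| 7 | 8–14 | 76 |

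The gap changes little: at k = 5 it is shorter by 5/83 = 6%. The window changes more: at k = 5 it shares only days 6 and 7 with that of a same-day admission, and at k = 7 it shares none.

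**Step 3: how the eligibility clock bears on step 2.** Under the onset rule, k is at most 1 (day-1 counting) or 2 (day-0 counting), so the window starts no later than post-stroke day 2 or 3. Under the admission rule, the article states no numerical cap on k; the only limiting word in Section 2.5 is that the stroke be acute. Aligning the eligibility text therefore bounds the shift under one clock and leaves it without a stated bound under the other.

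**The case against.** The strongest reply is that this is one loose sentence in an abstract. Screening, the inclusion criterion, the dose definition, the analysis text and Table 1 are all counted from admission, and sites can be expected to enroll from the criteria list. That is fair. A reader might infer that the twelve hospitals will apply different entry rules, but nothing in the article shows this. What stands is that both sentences are current text and describe different populations.

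A reader might also infer that counting dose from admission and outcome from onset is itself a contradiction, or that it materially shortens follow-up. Neither is supported. Each clock is used consistently for its own purpose, inpatient dose is naturally recorded from admission, and the change in the gap is small.

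On the missing cap and covariate, the article condenses a fuller protocol that may define acute in hours or days, and Section 2.14 introduces its covariates with an open-ended word. An analysis plan, not shown, could add the delay. The stated hypotheses concern dose and severity, no timing analysis is planned, and NIHSS and facility absorb some of the difference. So the absence of an onset limit is no finding in itself, and the covariate is an improvement to the named set rather than the correction of an error. It remains worthwhile because NIHSS at admission does not fully stand in for time since stroke.

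Finally, a reader might object that consent within 24 h of admission precedes verification of the day-2 criterion. That is ordinary sequencing: a consented patient who does not start in time simply fails the criterion.

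**Conclusion.** The point holds in two parts. The Abstract and Section 2.5 give different clocks for the same criterion, and the passages must be reconciled. The article does not settle which was intended, although its operational sections lean on admission. Separately, the dose window moves by k days relative to the stroke for a patient admitted k days late, and the named covariates do not account for this.

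In size, the rules can disagree from a one-day delay and always disagree from two or three days, depending on an unstated day-numbering convention. How many patients this touches cannot be computed, because no distribution of onset-to-admission times is given; any count would be an assumed share multiplied by the sample size. The direction and size of any confounding are also unknown. The argument assumes that delay is related to both achievable dose and outcome, which the Introduction's account of the acute phase makes plausible but does not demonstrate.

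**What to change.** 1. State the start-of-rehabilitation criterion with one clock, in identical words, in the Abstract and Section 2.5, and say whether the first day is day 0 or day 1. The choice of clock is for the investigators.
2. Add onset-to-admission time as a covariate in the primary logistic model in Section 2.14. It can be derived from two dates the study already needs: onset for the day-90 assessment and admission for the MQS window. It matters more if the admission clock is kept, since the delay then has no stated bound.

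The cost is a wording correction and one extra model parameter if the delay enters as a single linear term, with no new data collection. Section 2.1 schedules enrollment from June 2026, so both changes are easiest to make before the first patient is entered.

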For secondary outcomes, multivariable linear regression models will be used for continuous variables, such as the Barthel Index. A pre-specified subgroup analysis will be conducted to explore whether the effect of rehabilitation dose is modified by initial stroke severity. An interaction term between the MQS score and the severity category (defined by baseline NIHSS) will be introduced into the primary model.

Time-to-event outcomes will be analyzed using Kaplan–Meier curves and Cox proportional hazards regression models, adjusted for baseline characteristics. For survival analysis, patients will be stratified into groups based on quartiles of rehabilitation volume and pre-defined stroke severity categories. Missing data for covariates will be handled using multiple imputation under the missing-at-random assumption. The primary analysis will be based on the pooled results from the imputed datasets, with a complete-case analysis performed as a sensitivity analysis.

All statistical analyses will be performed using JMP (version 13.0; SAS Institute, Cary, NC, USA) and IBM SPSS software (version 23.0; IBM, Armonk, NY, USA). A two-sided *p*-value of <0.05 will be considered statistically significant.

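### Care-goal changes or deaths in days 1–7 can lower the mean MQS and worsen the outcome together, which can produce a spurious benefit of higher dose; no planned analysis checks this

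*Protocol article*

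**What the plan says.** **Entry.** Section 2.5 lists "Terminal care patients or those with non-curative intent" among the exclusions. Section 2.3 states that "All hospitalized stroke patients will be screened within 24 h of admission", and Table 1 marks the eligibility screen at admission only. Two inclusion criteria narrow the cohort further: patients "who are expected to be hospitalized for ≥7 days", and "Initiation of rehabilitation by day 2 of admission".

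**Retention.** Under Section 2.4, "patients will remain in the study until loss to follow-up or completion of the 90-day assessment post-onset". No rule in the article covers a change of care goal after enrolment. Table 2 records the date of death during follow-up.

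**Exposure.** Section 2.13 states: "The MQS is averaged across the first 7 days to reflect the daily rehabilitation dose". Only active time counts.

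**Outcome.** Section 2.6 scores death as mRS 6 and defines a favourable outcome as mRS 2 or less at 90 days.

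**Analysis.** Section 2.14 fits a logistic model adjusted for age, sex, pre-admission mRS, baseline NIHSS, stroke subtype and facility. For the severity question, "An interaction term between the MQS score and the severity category (defined by baseline NIHSS) will be introduced into the primary model". The only sensitivity analysis named is complete-case.

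**The concern.** Eligibility closes at about one day, but the exposure accrues over seven. If the care goal changes inside that window, active mobilization may be reduced or stopped, and an mRS of 2 or less at 90 days becomes very unlikely. The low dose then follows from the expected outcome and does not cause it. Admission covariates cannot remove this, because the decision reflects the course after admission. Complete-case analysis does not address it either, since these patients can have complete data.

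The direction is predictable: higher dose looks better. In severe stroke this runs against one of the protocol's own hypotheses, "whereas lower-intensity mobilization may be more beneficial in those with severe strokes". The Discussion also expects clinicians to derive dose targets by severity from these data. Both the primary dose estimate and the slope in severe patients are therefore exposed.

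**Working it through.** **The plan's own figure.** Section 2.14 expects at least 200 patients from at least 20 facilities with at least 10 each: 10 × 20 = 200, which reproduces. It is not a power calculation. (Sections 2.1 and 2.3 name twelve hospitals, which is a separate matter; 200 is used here because it is the stated size.)

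**Taken from the article.** MQS averaged over days 1–7; favourable outcome mRS ≤ 2 with death as 6; baseline-only adjustment; MQS × severity term; two-sided 0.05; N = 200.

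**Assumed, not in the article.**
- 25% of patients are severe: 200 × 0.25 = 50 severe and 150 non-severe.
- NIHSS is uniform on 16–30 in severe patients and 1–15 in the others.
- MQS = 12 − 0.3 × NIHSS + normal error with SD 2.5, floored at 0.3. The 2.5-point unit below is this SD.
- Log-odds of a favourable outcome = logit(p) − 0.12 × (NIHSS − c). Here p is 10% or 20% in severe patients (c = 23) and 65% in the others (c = 8). The true dose effect is zero.
- The care goal changes in 0–30% of severe patients and, whenever the severe share is above zero, in 1% of the others.
- After a change, mean MQS is multiplied by 0.3 × d/7 with d = 1 to 4, that is by 0.3 × 1/7 = 4% up to 0.3 × 4/7 = 17%. The outcome is set to unfavourable.

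The main-effect model contains MQS and NIHSS; the interaction model adds severity category and MQS × severity. Other covariates and the facility effect were left out. Odds ratios come from 400,000 simulated patients, and rejection rates from 1,500 cohorts of 200. Each cell shows p = 10% / p = 20%.

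| Severe patients changing | Severe OR per 2.5 points | Overall OR per 2.5 points | Main effect rejected | Interaction rejected |
|---|---|---|---|---|
| 0% | 1.01 / 1.00 | 1.00 / 1.00 | 5.3% / 5.5% | 3.9% / 4.1% |
| 5% | 1.11 / 1.12 | 1.10 / 1.10 | 9.3% / 10.2% | 2.7% / 3.9% |
| 10% | 1.21 / 1.22 | 1.12 / 1.12 | 12.2% / 12.6% | 2.7% / 4.0% |
| 20% | 1.33 / 1.41 | 1.15 / 1.17 | 15.4% / 16.8% | 2.5% / 6.3% |
| 30% | 1.50 / 1.57 | 1.18 / 1.20 | 18.4% / 23.5% | 4.1% / 11.1% |

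**Counts at N = 200.** A 5% share is 50 × 0.05 = 2.5 severe patients, plus 150 × 0.01 = 1.5 others: about four in all. A 30% share is 15 + 1.5 = 16.5.

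**Non-severe patients.** Their odds ratio is 1.09–1.11 in every row above 0%, from a 1% share alone. The overall figures therefore depend on that 1% as well as on the severe share.

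**After removing the patients who changed.** The severe odds ratio is 0.98–1.01 in every row. This is partly by construction, because change was simulated independently of the remaining prognosis within stratum.

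**The case against.** **The exclusion itself is in order.** Applying an entry criterion at entry is normal practice, and Section 2.3 with Table 1 already makes the timing clear. The article does not say why these patients are excluded, so the criterion cannot be read as admitting that their dose–outcome comparison is meaningless. This stands. The point concerns exposure and analysis.

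**The affected group is limited.** Rehabilitation must have started by day 2 and a stay of at least 7 days must be expected, so a patient whose goal changes before any rehabilitation is not eligible. This stands. The filters shrink the group, but they do not remove patients whose course changes later in the week.

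**A reader might infer that these patients have near-zero MQS.** The article does not support that. With level daily dosing and no activity from the day of change, a day-3 change leaves 2/7 = 29% of the mean and a day-5 change 4/7 = 57%. The simulated cut to 4–17% is stronger. A dose that rises over the week would lower those fractions, but no trajectory is given. The article also does not say that mobilization stops when the goal changes, or how days after a death enter the mean. A milder cut would give a smaller bias.

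**A reader might infer a false severity interaction, or harm confined to severe stroke.** Neither is supported. The interaction test rejects in only 2.5–11% of cohorts, and the overall estimate also moves.

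**This may be detail for the full protocol or SAP, and the Discussion concedes that causality cannot be established.** This stands in part. The article does fix the exposure window, covariates and sensitivity analysis, and these together leave the bias unexamined. The general caveat names neither this route nor its direction. An analysis plan also cannot use a date that was not collected, and no item described in the article captures it.

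**Other post-admission events can confound dose too.** True. This route is one of several, but it can be checked at little cost.

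**Conclusion.** The concern holds as a possible bias of known direction and unknown size. As described, the plan lets a change of care goal or a death in days 1–7 lower the exposure and determine the outcome together, with only baseline adjustment. This can create a spurious benefit of higher dose in the overall primary estimate and in the slope for severe stroke.

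Under a true null, with 5–30% of severe and 1% of other patients assumed to change and a strong cut in MQS, the severe-stratum odds ratio is about 1.1–1.6 per 2.5 points and the overall odds ratio 1.10–1.20. The main-effect false-positive rate is about 9–24% at N = 200, against about 5% with no changes.

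The article gives no frequency of such changes, so it does not support saying that a false benefit will occur. The upper figures require a large share of already filtered patients to change within a week. This is a worthwhile, inexpensive improvement to the plan.

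**What to change.** 1. Record the date of any change to terminal or non-curative care, alongside the date of death already collected.
2. Pre-specify a sensitivity analysis that repeats the primary model and the MQS × severity model in patients who are alive and without such a change at day 7 (a day-7 landmark). Report it beside the primary analysis.
3. State in advance that a dose conclusion, overall or in severe stroke, that does not persist in this analysis will be reported as possibly due to reverse causation.

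Averaging MQS only over the days before the change is a less suitable alternative, because it sets a mean over the earliest days against full seven-day means.

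The cost is one date field and two further model fits, and enrolment is not due to start until June 2026. The downside is that a few patients are removed on a post-entry event. That can itself introduce selection, so the landmark analysis should remain a sensitivity analysis and not replace the primary one.
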